### Research instruments

A household survey instrument was implemented prior to baseline to determine eligibility for the intervention and for selecting cases in designated control clusters. The household instrument included a roster of all household members with basic socio-demographic information on each member, household asset ownership, housing quality, recent household shocks, access to financial resources and distances to key resources, including schools, roads, health facilities, banks, etc. Comprehensive annual surveys were conducted at baseline and for four subsequent years. The baseline survey is included as an Additional file 1. The surveys instruments measure changes in attitudes, behaviour, transition status, social assets and cognitive skills that may occur over time regarding: educational attainment and schooling transitions; sexual activity, relationship status and sexual partners; marriage and marital dissolution; sexual and physical coercion and violence; gender attitudes, self- efficacy and locus of control; labour force participation and savings behaviour; living arrangements and household resources; mobility and migration; literacy, numeracy and cognitive skills; and ability; financial literacy and knowledge. Surveys conducted after the baseline also include questions of exposure to the intervention to address potential spillover impacts. All questionnaires were translated into Nyanja, Bemba and Kaonde.

Survey instruments were implemented by electronic data capture. Computer-Assisted Personal-Interviewing (CAPI) was used for questions that are non-sensitive. CAPI is a process of data capture in which the interviewer reads the question from a computer screen and enters the participant’s response directly into a handheld or tablet device. For sensitive questions, including sexual behaviour, sexual violence, HIV risk perception, unwanted pregnancy and abortion, Audio Computer-Assisted Self-Interviewing (ACASI) was used. With ACASI the respondent listened with headphones to pre-recorded questions and response categories, while, if desired and if the participant was literate, simultaneously reading the question on the device screen. The participant entered a response by touching a designated number or option. ACASI maximizes confidentiality and privacy of response, as no one could hear or see the question being read, nor the response option selected.

Biological markers were collected from adolescents aged 15 and older at baseline (Round 1), after Round 3 (at the end of AGEP), and Round 5 (at the end of the evaluation). HIV status was determined via capillary blood draws obtained from finger pricks. HIV tests were conducted by trained and certified voluntary counselling and testing (VCT) staff. In accordance with Ministry of Health guidelines, we conducted serial testing using Determine™ and Uni-Gold™ [27]. Both tests have a very high sensitivity (100%) and specificity (>99%) in controlled clinic evaluations, including a controlled laboratory setting in rural Kenya [28]. The respondent was provided the test results. Post-test counseling was guided by National Guidelines for Testing and Counselling [29].

The HSV-2 biological specimens were collected via finger prick. A sample of whole blood was collected and stored in microtainers and laboratory tested. To conduct the laboratory test, serum was derived from the whole blood and the Kalon ELISA assay used, for which the sensitivity and specificity have been found to be high (92% and 98%) respectively in African populations when compared to Western Blot [30]. Indeterminate results were not retested since their prevalence was so low as to make it impractical. After specimen collection all participants were provided information about HSV-2 detection, symptoms, safe sex practices and treatment options. Respondents were provided vouchers with identification numbers to receive their test results at AGEP participating health centers. A validation of the HSV-2 laboratory testing procedures was conducted prior to testing of specimens for the main study to assure the quality of laboratory testing protocols.

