The minimally detectable effect sizes were estimated for comparison of each programme component against the control; estimates of effect sizes were not obtained for comparisons between the intervention arms themselves as little prior information was available to guide such an estimation approach. Given a total of ten study sites, it was determined that a total of 40 clusters per arm (four clusters per arm per site) and 20 participants per cluster was the most efficient combination. Baseline (control) estimates of study indicators by age group and residential status were obtained from the 2007 Zambia Demographic and Health Survey [26]. Statistical power of 0.80 and an alpha coefficient of 0.05 were set, while the effect size variability was fixed at 0.00, as analyses would control for site fixed effects [25]. Table 5 provides estimates of prevalence in the control sample and minimal detectable effect sizes, by outcome and study stratifications.

**Table 5 Tab5:** Estimates of prevalence in the control and minimally detectable effect sizes in percentage points (pp) of programme impact by age-cohort and by rural and urban stratifications

	Total^a^		Rural^b^		Urban^b^	
	Younger	Older	Younger	Older	Younger	Older
Ever had sex	40%, ± 10 pp	82%, ± 9 pp	47%, ± 14 pp	89%, ± 11 pp	34%, ± 13 pp	75%, ± 13 pp
Ever married	15%, ± 6 pp	63%, ± 10 pp	19%, ± 11 pp	76%, ± 13 pp	10%, ± 8 pp	48%, ± 14 pp
Ever given birth	16%, ± 6 pp	70%, ± 10 pp	18%, ± 10 pp	83%, ± 13 pp	13%, ± 8 pp	54%, ± 14 pp
Completed grade 7	61%, ± 10 pp	60%, ± 9 pp	43%, ± 14 pp	41%, ± 15 pp	79%, ± 11 pp	85%, ± 9 pp
Completed grade 9	28%, ± 10 pp	38%, ± 10 pp	11%, ± 11 pp	17%, ± 13 pp	45%, ± 15 pp	64%, ± 14 pp
Ever use of modern contraception	15%, ± 8 pp	55%, ± 7 pp	15%, ± 12 pp	55%, ± 14 pp	15%, ± 12 pp	55%, ± 15 pp
HIV prevalence	6%, ± 4 pp	12%, ± 6 pp	6%, n/a ^c^	7%, n/a ^c^	6%, n/a ^c^	19%, ± 10 pp
HSV-2 prevalence	21%, ± 8 pp	26%, ± 8 pp	21%, ± 11 pp	26%, ± 12 pp	21%, ± 11 pp	26%, ± 12 pp

*Notes*: Younger cohort members are expected to be ages 14–18 at endline; older cohort members are expected to be ages 19–23 at endline. All estimates assume alpha of 0.05, power of 0.80, and site fixed effects

^a^For each age cohort estimates are based on: 10 sites, 4 clusters per arm per site (40 clusters per arm), and 10 subjects per cluster

^b^For each age cohort estimates are based on: 5 sites, 4 clusters per arm per site (20 clusters per arm), and 10 subjects per cluster

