^c^Not powered at 0.80 to detect programme impact

The sample size calculations indicated that 3200 girls would be needed at the end of the study to assess all key study impact indicators: 800 girls (within 40 study clusters) in each of the three AGEP arms and in the control arm. An additional 400 girls (within 20 clusters) were designated to be sampled for urban areas in nearby high-density components. These girls and clusters were designed to serve as external controls given the potential for contamination between AGEP and control girls within the same site. Never married girls were targeted at baseline as a significant proportion of older girls would have already experienced the key outcomes that were meant to be impacted by the programme. To achieve the target sample of 3600 girls at the end of the study, the sample size was inflated for non-eligibility and non-response at baseline, attrition from the cohort and refusals for biological specimen collection. Thus, the final estimated sample to be collected at baseline was 7200 or 4800 in AGEP clusters, 1600 in internal control clusters and 800 in external control areas.

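### Table 5's younger-cohort HIV and HSV-2 cells count 10 girls per cluster aged 14–18, but girls under 15 are not tested, so their stated power is not supported as written

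*Protocol article*

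**What the plan says.** Two parts of the protocol article bear on this.

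- **Research population and sample sizes, Table 5.** The younger cohort (10–14 at baseline) has a stated detectable effect in four biomarker cells: HIV Total (control 6%, 4 pp), HSV-2 Total (control 21%, 8 pp), and HSV-2 Rural and Urban (control 21%, 11 pp each). Younger-cohort HIV in Rural and Urban is n/a, with the footnote "Not powered at 0.80 to detect programme impact". The Total cells rest on "10 sites, 4 clusters per arm per site (40 clusters per arm), and 10 subjects per cluster" and the stratum cells on "5 sites, 4 clusters per arm per site (20 clusters per arm), and 10 subjects per cluster". The table note adds "Younger cohort members are expected to be ages 14–18 at endline" and "All estimates assume alpha of 0.05, power of 0.80, and site fixed effects".
- **Research instruments.** Specimens have an age floor: "Biological markers were collected from adolescents aged 15 and older at baseline (Round 1), after Round 3 (at the end of AGEP". The same sentence goes on to name Round 5 as the third collection time.

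The sample-size section also says that the baseline sample was enlarged to 7200 to cover baseline non-eligibility and non-response, cohort attrition, and refusal of specimens. It does not list girls below the testing age at endline.

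**The concern.** A detectable effect for HIV or HSV-2 can rest only on girls who give a specimen. By the table's own note, the younger cohort at endline includes 14-year-olds, who fall below the floor. Nothing in the article reconciles the two statements.

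The size of the problem depends on what the floor means. If it is age 15 or older at each collection round, the loss at Round 5 is the girls who were 10 at baseline. If it is age 15 or older at baseline, no girl from the 10–14 cohort is ever tested.

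HIV and HSV-2 prevalence are longer-term outcomes in Table 4, and the Abstract names both infections among the outcomes for which the study was powered. A reader of Table 5 would take the younger cohort as adding an 80%-power comparison on each. The Round 5 assessment is still prospective in this article.

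**Working it through.** **Inputs from the article.** Alpha 0.05 and power 0.80. Each arm has 40 clusters (Total) or 20 (Rural or Urban), with 10 younger girls per cluster at endline. Control rates are 6% (HIV) and 21% (HSV-2).

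**Assumptions.** Two-sided test; an ICC of 0 to 0.02 (the article gives none); ages spread evenly over 14–18 at endline; control rates as printed. The tested subset is slightly older, so its control rate may differ, but the article gives no figure for it.

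**Formulas.** Effective n per arm = k·m / [1 + (m − 1)·ICC], with k clusters and m girls per cluster. For a reduction d from p1 to p2, with p̄ their mean:

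Power = Φ{ [d − 1.96·√(2p̄(1 − p̄)/n)] / √([p1(1 − p1) + p2(1 − p2)]/n) }

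**Step 1: reproduce Table 5 with m = 10.** For HIV Total at ICC 0.01, n = 400/1.09 = 367.0. Power at 4 pp = Φ[(0.04 − 1.96 × 0.01447)/0.01439] = Φ(0.81) = 0.79. Solving for 80% power gives:

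| Cell | ICC 0.01 | ICC 0.02 | Printed |
|---|---|---|---|
| HIV Total | 4.04 pp | 4.17 pp | 4 pp |
| HSV-2 Total | 7.78 pp | 8.06 pp | 8 pp |
| HSV-2 Rural, Urban | 10.61 pp | 10.98 pp | 11 pp |

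All round to the printed values, so the table is consistent with counting all 10 girls, including those aged 14. The match holds for reductions only. For increases at ICC 0.01 the values would be 5.9, 9.0 and 13.0 pp.

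**Step 2: apply the age floor at each round.** Four of the five ages from 14 to 18 can be tested, so m = 10 × 4/5 = 8. That is 320 girls per arm (Total) or 160 (stratum). For HIV Total at ICC 0.01, n = 320/1.07 = 299.1 and power at 4 pp = Φ[(0.04 − 1.96 × 0.01602)/0.01594] = Φ(0.54) = 0.705.

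| Cell (printed effect) | Power, ICC 0 / 0.01 / 0.02 | Detectable reduction, ICC 0 / 0.01 / 0.02 |
|---|---|---|
| HIV Total (4 pp) | 0.734 / 0.705 / 0.677 | 4.26 / 4.38 / 4.49 pp |
| HSV-2 Total (8 pp) | 0.770 / 0.742 / 0.714 | 8.28 / 8.53 / 8.78 pp |
| HSV-2 Rural, Urban (11 pp) | 0.779 / 0.750 / 0.723 | 11.26 / 11.59 / 11.91 pp |

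For comparison, power with all 10 girls at ICC 0.01 is 0.791, 0.824 and 0.832. The loss from the age floor is therefore about 8 to 9 percentage points of power.

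**Step 3: apply the floor at baseline.** All younger girls are 10–14 at baseline, so m = 0 and the cells have no sample.

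**Step 4: can the baseline inflation cover the loss?** AGEP clusters have 4800/120 = 40 girls each at baseline. The article does not split this by age cohort.

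- *Equal split (assumed).* 20 × 0.80 retained × 0.80 aged 15 or older = 12.8 before baseline ineligibility, non-response and refusal. Ten tested girls need a yield of 10/12.8 = 78% after those losses.
- *Each cohort sized to end with 10 girls, using its own stated attrition (20% and 35%) and a common yield y.* The younger cohort needs 10/(0.80y) = 12.5/y recruits and the older 10/(0.65y) = 15.4/y. After the age floor the younger cohort has (12.5/y) × 0.80 × y × 0.80 = 8 tested girls, so the inflation leaves nothing spare.

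**The case against.** The strongest objection is that 10 per cluster is an analysis input, not the number recruited. Under an equal split the younger cohort needs a 78% yield to reach 10 tested girls. The older cohort, with 20 × 0.65 = 13 retained, needs 10/13 = 77%. The younger cohort without its 14-year-olds would then have almost the margin that the design accepts for the older cohort. This stands as a possibility, but the equal split is an assumption and the second allocation in the working leaves 8. The article shows neither.

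The effect is also modest. In whole points the HIV cell stays at 4 pp, and each HSV-2 cell moves by at most one point (8 to 9, 11 to 12), or not at all at ICC 0. Part of the gap below 0.80 for HIV comes from rounding in the table, since power at exactly 4 pp is 0.79 with all 10 girls at ICC 0.01. Both remarks stand.

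A reader might go further and infer that the four cells cannot be delivered at all. That needs the floor to mean age at baseline. The Table 1 footnote does use a fixed baseline-age rule for some nutrition sessions, so the reading cannot be excluded. In Research instruments, however, baseline is the first of three listed collection times. Attaching it to the age limit would remove baseline as a time of collection. Age 15 or older at each round is the more natural reading, and it also fits a table that gives biomarker effects for this cohort at endline.

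**Conclusion.** The point holds in a limited form. Four cells state 80% power on 10 girls per cluster, while the stated testing rule excludes some of the girls counted and the stated inflation does not provide for them. Under the more natural reading the shortfall is moderate: power of about 0.68–0.78 at the printed effects, and detectable reductions of about 4.3–4.5 pp (HIV Total), 8.3–8.8 pp (HSV-2 Total) and 11.3–11.9 pp (HSV-2 Rural and Urban). These figures rest on an even age spread, no spare recruitment, a two-sided test and an ICC of 0–0.02. Spare baseline recruitment could remove part or all of the shortfall. The sample is zero only if the floor is age at baseline.

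A reader might also infer that the Abstract's statement about power for HIV and HSV-2 fails. The age floor does not touch the older-cohort cells, so the article does not support that. Younger-cohort HIV in Rural and Urban is already marked as not powered and is outside this point.

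**What to change.** State in Research instruments whether the age floor applies at baseline or at each specimen round.

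- **At each round:** restate the four younger-cohort cells and their footnotes on the number of girls expected to be 15 or older at Round 5. Alternatively, give the baseline split by cohort and show that the inflation still yields 10 tested younger girls per cluster.
- **At baseline:** delete the four cells and declare HIV and HSV-2 as outcomes of the older cohort only.

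This takes one sentence and four table cells with their footnotes. Under the each-round reading the cost is slightly less favourable stated detectable effects, and nothing in the conduct of the trial changes. Under the baseline reading the cost is the younger cohort's biomarker claims.

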### Economic evaluation

The study also includes an economic evaluation to rigorously assess the cost of implementing AGEP, as well as to assess the incremental cost-effectiveness of the add-on components (health voucher and savings account) relative to the girls group intervention alone.. Direct programme costs were collected from AGEP budgets and financial reports and included both start-up and programme delivery costs for the Population Council and its partners. Participant-specific out-of-pocket and indirect costs data for participation in AGEP and uptake of services were also obtained. The relevant costs for these analyses are the real resource costs of delivering the programme services, not including the costs related to project evaluation. A decision analytic model will be constructed to generate estimates of the incremental costs per negative health outcome averted and positive progress achieved on non-health indicators from participating in AGEP. Incremental cost-effectiveness ratios (ICERS) comparing the add-ons to the girls group only intervention will be calculated to assess whether cost-effectiveness varies by study arm.

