**Methods/design:**

AGEP was a multi-sectoral intervention targeting over 10,000 vulnerable adolescent girls ages 10–19 in rural and urban areas, in four of the ten provinces of Zambia. At the core of AGEP were mentor-led, weekly girls’ group meetings of 20 to 30 adolescent girls participating over two years. Three curricula ― sexual and reproductive health and lifeskills, financial literacy, and nutrition ― guided the meetings. An engaging and participatory pedagogical approach was used. Two additional program components, a health voucher and a bank account, were offered to some girls to provide direct mechanisms to improve access to health and financial services. Embedded within AGEP was a rigorous multi-arm randomised cluster trial with randomization to different combinations of programme arms. The study was powered to assess the impact across a set of key longer-term outcomes, including early marriage and first birth, contraceptive use, educational attainment and acquisition of HIV and HSV-2. Baseline behavioural surveys and biological specimen collection were initiated in 2013. Impact was evaluated immediately after the program ended in 2015 and will be evaluated again after two additional years of follow-up in 2017. The primary analysis is intent-to-treat. Qualitative data are being collected in 2013, 2015 and 2017 to inform the programme implementation and the quantitative findings. An economic evaluation will evaluate the incremental cost-effectiveness of each component of the intervention.

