### Randomised cluster design

The AGEP evaluation was designed as a multi-arm randomised cluster trial where clusters within the ten study sites were randomised to receive different combinations (arms) of AGEP. The experimental and control arms of the study are displayed in Table 3, along with their associated components. Clusters assigned to the first intervention arm were assigned only the weekly girls’ group sessions. Clusters in the second intervention arm were assigned the health voucher in addition to the weekly girls’ group sessions, while clusters in the final intervention arm were assigned all components, including the bank account. The multi-arm evaluation provided for a rigorous assessment of the marginal benefit, as well as the incremental cost-effectiveness of each additional component of the intervention. All girls selected for participation in AGEP within a cluster were assigned to the intervention that was randomly selected for that cluster; girls in clusters for the control arm received neither interventions nor placebo exposures.

**Table 3 Tab3:** Randomisation arms of AGEP

Study arm	AGEP components
Intervention arm 1	Weekly girls group mentor-led sessions
Intervention arm 2	Weekly girls group mentor-led sessions + health voucher
Intervention arm 3	Weekly girls group mentor-led sessions + health voucher + bank account
Control	No components of the AGEP intervention

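### Girls' groups only is named as comparator for both add-ons, so the bank account's cost-effectiveness ratio would be that of voucher and account together

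*Protocol article*

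**What the plan says.** The arms are nested (protocol article, Randomised cluster design, Table 3):

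- Arm 1: "Clusters assigned to the first intervention arm were assigned only the weekly girls’ group sessions".
- Arm 2: "Clusters in the second intervention arm were assigned the health voucher in addition to the weekly girls’ group sessions".
- Arm 3: "Weekly girls group mentor-led sessions + health voucher + bank account".

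No arm offers the account without the voucher. The same section says that the multi-arm design allows assessment of the marginal benefit and the "incremental cost-effectiveness of each additional component of the intervention". The abstract goes a little wider: "An economic evaluation will evaluate the incremental cost-effectiveness of each component of the intervention".

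The Economic evaluation section names one comparator for both add-ons, and does so twice. The aim is the "incremental cost-effectiveness of the add-on components (health voucher and savings account) relative to the girls group intervention alone". The method then reads: "Incremental cost-effectiveness ratios (ICERS) comparing the add-ons to the girls group only intervention will be calculated". The purpose attached to that sentence is to see whether cost-effectiveness differs between arms. The article nowhere mentions a ratio for arm 3 against arm 2.

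**The concern.** The aim is framed per added component, but the comparator is fixed at groups only for both add-ons. For the voucher the two agree, because arm 2 differs from arm 1 by the voucher alone. For the account they do not, because arm 3 differs from arm 1 by the voucher and the account together.

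The Discussion says that the economic results are meant to inform scale-up and the cost of investing in each component. A ratio that pools the two add-ons but is read as the account's could make a poor account look acceptable because the voucher works, or a good account look poor because the voucher does not.

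**Working it through.** **Inputs.** The arm contents come from Table 3. The article gives no cost, effect or ratio, so there is no figure to reproduce, and all numbers below are assumed for illustration.

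Let Cv and Ev be the cost and effect per girl that the voucher adds to the groups. Let Cb and Eb be what the account adds to groups plus voucher. Effect is negative outcomes averted per girl.

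**Formulas.**

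- Arm 2 v arm 1 = Cv/Ev (voucher).
- Arm 3 v arm 2 = Cb/Eb (account, given the voucher).
- Arm 3 v arm 1 = (Cv + Cb)/(Ev + Eb) (both together).

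Setting the third equal to the second gives Cv × Eb = Cb × Ev. With Eb not zero, this holds only if Cv/Ev = Cb/Eb, or if Cv and Ev are both zero. When both effects are positive, arm 3 v arm 1 is the mean of the two component ratios, weighted by their effects. It therefore overstates the account's ratio when the account is better value than the voucher, and understates it when the account is worse value.

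**Illustration.** Assume Cv = 20 and Cb = 10 throughout.

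| Ev | Eb | Arm 2 v arm 1 | Arm 3 v arm 1 | Arm 3 v arm 2 |
|---|---|---|---|---|
| 0.04 | 0 | 20/0.04 = 500 | 30/0.04 = 750 | added cost, no gain |
| 0.04 | 0.005 | 500 | 30/0.045 = 667 | 10/0.005 = 2000 |
| 0.04 | 0.01 | 500 | 30/0.05 = 600 | 10/0.01 = 1000 |
| 0.04 | 0.04 | 500 | 30/0.08 = 375 | 10/0.04 = 250 |
| 0.01 | 0.04 | 20/0.01 = 2000 | 30/0.05 = 600 | 250 |

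In the first three rows the comparison with groups only flatters the account. In the last two it penalises the account. In the first row an account with no effect still receives a finite ratio.

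**Where the package ratio does belong.** In the last two rows the ratio falls from the first step to the second, so arm 2 is extendedly dominated. The ratio for choosing among the arms actually trialled is then arm 3 v arm 1. That ratio still values the pair; what the account adds is the figure in the last column.

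**The case against.** The best defence is that one sentence in a condensed article refers to the add-ons collectively and names no pair of arms. The stated design aim suggests a stepwise reading, and a fuller plan may list the comparisons and dominance rules. Part of this stands: nothing irreversible has been fixed. If the cost and effect differences of arms 2 and 3 against arm 1 are reported, arm 3 v arm 2 follows by subtracting them. The ratios alone do not allow that subtraction. The point is also not about missing detail, since the comparator is stated twice and does not fit the stated aim.

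A common comparator does describe whether cost-effectiveness differs by arm, which is the purpose given in that sentence. It does not give the added value of each component.

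Precision is a fair concern. The section on research population and sample sizes says that detectable effects were not estimated for comparisons between intervention arms, and a small effect difference in the denominator makes a ratio unstable. But arm 3 v arm 1 is also a comparison between intervention arms, so this is no reason to prefer it.

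A reader might also infer that the girls' groups themselves get no ratio, because groups only is the sole comparator named for the ratios. The documents do not support that. The same section plans a model of incremental cost per outcome from taking part in AGEP, which is naturally read as against no programme, and the Discussion promises cost-effectiveness information for every arm. The design section's promise covers additional components only.

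**Conclusion.** The concern holds for the bank account and for nothing else in the economic plan. As worded, the comparator does not deliver the account's incremental cost-effectiveness, which the design section and the abstract promise. The voucher's comparison is right, and the design can answer the account question, because arm 3 v arm 2 is a randomised contrast.

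The algebra rests only on the nesting in Table 3. The direction and size of the error cannot be known from the documents, and the figures above show only that it can go either way.

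One limit remains under any wording. Because no arm has the account without the voucher, the account's ratio is conditional on the voucher being present. Its ratio on top of groups alone cannot be estimated from any arm contrast without assuming that the two components act additively.

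This is an economic analysis rather than the primary impact analysis, but its results are meant to guide investment by component, so the wording should be corrected.

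**What to change.** In the Economic evaluation section, in both the aim and the sentence on ratios, state sequential comparisons for the add-ons:

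- arm 2 v arm 1 for the voucher;
- arm 3 v arm 2 for the account, described as its value given groups and voucher;
- checks for dominance and extended dominance across the arms;
- arm 3 v arm 1 kept only if labelled as the combined voucher-and-account package.

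Report the cost and effect differences behind each ratio, with their uncertainty.

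The cost is a change of wording, since the same cost and effect data are used. The small downside is that the arm 3 v arm 2 ratio may be imprecise, as no detectable effect was derived for comparisons between intervention arms. The report should say so and should not rest on the point estimate alone.
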